### Data management

Completed personal data or other documents containing protected personal health information will be kept in a locked file at the principal investigator office in every center. Data will be entered into an electronic de-identified database (RedCap) by authorized study team members and checked for completeness and accuracy. Access to data with identifiers will be restricted to authorized study team members and authorities. Electronic data will be kept on a server regulated by the local research institute (IDISNA).

Data will be destroyed 10 years after study finalization or 5 years after last publication.

### Detailed description of the intervention

#### Usual care group (control group)

Participants randomized to the control group will receive normal outpatient care in the Fall Unit. Briefly, it includes a detailed multidimensional assessment performed by the multidisciplinary team (geriatrician, nurse, physiotherapist, occupational therapist) to identify potential intrinsic and extrinsic factors related with falling. Frequently, causality of falling is multifactorial and interventions in the Falls Units are based on the identification of individual risk factors. General approach includes medical review of high risk of falling medications, nutritional interventions like vitamin D in deficient patients, environmental modifications and prescription of the OEP, deemed the gold-standard exercise program in falls management and therefore, part of the usual care delivered to frail older fallers.

Subjects in this group will partake in a home-based exercise program based on the OEP lasting 12-weeks. A physiotherapist will provide a comprehensive explanation of the program, as well as fall risk, safety and adherence information at the baseline visit and will monitor progression during the study visits. Subjects will be encouraged to perform cardiovascular, strength, flexibility and balance exercises 3-times/week. Both volume and intensity will be adjusted by the physiotherapist based on participant’s self-reported feelings. Subjects will be provided with a booklet with instructions (Additional File 1) and an adherence log (Additional File 2) that will be filled in by the participant or a proxy.

#### Intervention group (VIVIFRAIL-COGN)

Participants assigned to this group will participate in a 12-week home-based program combining the VIVIFRAIL multicomponent physical exercise and an individualized cognitive training programme (VIVIFRAIL-COGN).

B1- Multicomponent VIVIFRAIL exercise group

The multicomponent physical exercise program will be based on the VIVIFRAIL programme which was developed in Europe (Erasmus + programme of the European Union).

The VIVIFRAIL multicomponent exercise intervention program includes individualized sets of resistance training, gait and balance training, which appear to be the best strategy for falls rate reduction in older individuals and to maintaining functional capacity during ageing [78]. This type of intervention has also been proven as the most effective to delay disability, cognitive impairment and depression [79] as well as effective to reverse the functional decline associated with acute hospitalization in very old patients [71]. The VIVIFRAIL exercise program was originally designed with the aim of providing guidance in exercise prescription to professionals managing frail older adults with or without falls older than 70 years [78]. The programme is tailored to the older person’s functional capacity evaluated by the SPPB and a UGS test and the risk of falling, aligning with the new functional-based older adult’s health perception proposed by the WHO [70] Different standardized programs oriented to the functional level of the individual were designed and description of the performance, intensity, volume, frequency and monitoring are described in the materials published. Recently, a new user-friendly simplified version and a simple mobile app with interactive videos have been produced to ease adoption and maximize adherence. (see www.vivifrail.com).

In VIVIFRAIL, subjects are assessed before the start of participation to rule out the presence of any contraindication to exercise (see above). Afterwards, functional capacity is assessed by means of physical performance tests to classify the older individual into one of the four exercise programs proposed. These physical performance tests are the SPPB and the 6-m UGS test (Table 2) with each leading to the recommendation of a certain customized multicomponent physical exercise program (see Table 2). If a high risk of falling is detected by the presence of recurrent falls (≥ 2 falls in the previous year or at least one fall requiring medical attention), reduced performance in the Up-and-Go Test (≥ 20 s) or the UGS (< 0.8 m/s) or a diagnosis of dementia, the balance component of the program is reinforced (indicated by the addition of “ + ” to the program name).

**Table 2 Tab2:** Exercise programs based on individual functional status assessed through the physical performance-based tests

SPPB Score	6-m UGS Test	Exercise Program^a^
0–3	< 0.5 m/s	A-Disability
4–6	0.5–0.8 m/s	B-Frailty
7–9	0.9–1 m/s	C-Pre-frailty
10–12	> 1 m/s	D- Robustness

^a^If a high risk of falling is detected: TUG (≥ 20 s), UGS (< 0.8 m/s), diagnosis of dementia and/or recurrent falls/falls requiring medical attention in the last year, subjects will be assigned to the “ + ” program, making emphasis on balance training

Once the individual has been assigned to an exercise program, they will partake in a 12-week exercise program with a frequency of 3 sessions/week. All the programs in Vivifrail share the following characteristics:

Resistance training:

▪ Sets and repetitions

Subjects will be encouraged to perform 3-4 exercises (depending on the program), with a volume of 3 series of 12 repetition. A 1 to 3 minute-break will be encouraged between exercises.

▪ Intensity and progression:

The intensity will be that allowing the completion of all the series with a feeling of moderate effort at the end of each series. Resistance will be adjusted accordingly along the duration of the program.

Cardiovascular training:

▪ Volume

Walking activities-based cardiovascular training will be recommended to improve cardiorespiratory fitness. Depending on the functional capacity of the individuals, walking bouts ranging from 5-10 seconds to 45 minutes will be prescribed.

▪ Intensity and progression

Subjects will be instructed to maintain a moderate effort during walking bouts and to progressively increase both the duration and the cost of walking.

Balance training:

Balance training will include both static and dynamic exercises adapted to individual abilities of the person.

▪ Volume

During static exercises, subjects will be instructed to remain in the same position for ten seconds in different conditions (one-foot stand, semi-tandem stand with eyes open/closed or in unstable surfaces). After resting, they will repeat three times.

In the case of dynamic exercises, subjects will perform different tasks (walking over obstacles, in different directions, paying attention to external stimulus…) in different conditions that should challenge their balance by demanding postural corrections. They will repeat the task 2-3 times.

In the case of the presence of high risk of falling (see above) the number, frequency and volume of balance exercises is increased.

▪ Intensity and progression

Subjects will progress towards more challenging situations (both in terms of feature of the exercises, difficulty or conditions) when current exercises do not require enough effort from them.

Safety recommendations will be provided to prevent falls during balance exercises.

Flexibility

Subjects will be instructed to perform a series of stretching exercises at the end of the sessions.

▪ Volume

They will perform 2-3 stretching exercises, with 2-3 repetitions per exercise lasting 10 seconds. They will be told to stretch until they feel a bit of tension and remain in the same position without discomfort.

Materials will be provided to allow correct execution and progression of the exercises and to maximize adherence. The latest Vivifrail update includes a passport-like booklet that allows to follow the session and have access to the graphical and textual descriptions of the exercises, as well as information relative to volume, frequency, intensity, and duration. In addition, it includes a section for registering adherence and the adherence log, respectively (see www.vivifrail.com).

During the baseline visit, the participant and a proxy will be informed about the features of the program and potential side effects, as well as safety and adherence measures and booklet functioning. The research team will also provide adaptable ankle weights.

B2-Cognitive training

The cognitive training program will last 12 weeks as well and will consist in twice weekly sessions combined with the above-mentioned physical exercise program (Table 3). Before the start of the intervention, cognitive status will be assessed through a global cognition test -Montreal Cognitive Test (MoCA) [80]- in order to individualize cognitive training exercises with the aim of maximizing benefits. The MoCA is a screening test with scores from 0 (worse cognitive function) to 30 (better cognitive function) and assesses different cognitive functions (including executive functions). In addition, adds other type of tasks as the clock test, a part of the Trail Making Test (part B), verbal fluency and denomination, items normally evaluated in a general assessment of cognition. For all these reasons the MoCA test is consider a more complete and sensitive screening test in older adults to monitor intervention than Mini-mental State Examination( MMSE) [81].

**Table 3 Tab3:** Within cognitive session structure:

Session = Set A + Set B
**Set A:** Set of attentional activities: A.1.) An exercise of sustained or selective attention with visual or auditive stimulus An exercise of dual or divided attention A.2.) An exercise of sustained or selective attention with visual or auditive stimulus An exercise of alternating attention
**Set B:** Set of executive function activities: B.1.) Processing speed and preceptive organization B.2.) Working memory and high attention system B.3.) Comprehension, abstraction and verbal reasoning B.4.) Planification, execution and problem solving (decision making and temporary estimation)

Based on the score of the MoCA and normative values in the Spanish population over 75 [81] years old, subjects will receive an intervention from the following:Program A. MoCA 26–30. High cognitive performance. Normal cognitive functionProgram B. MoCA 20–25. Intermediate cognitive performance. No evidence of clinical cognitive declineProgram C. MoCA 13–19. Low cognitive performance. Mild cognitive declineProgram D. MoCA ≤ 12. Very low cognitive performance. Mild dementia

In every session a combination of one exercise from Set A (attentional activities) and one exercise from Set B (executive function activities) will be performed (see Table 3). An initial training session will be performed to explain the programme to the participants and their relatives or caregiver (the support of one person during sessions will be needed due to characteristics of the cognitive training exercises).

To guarantee adherence to the program and appropriate execution of cognitive training exercises, a videoconference session will be performed at week 3 and 9 of the program by the occupational therapists. The purpose of this monitoring is to resolve doubts, adapt difficulty and provide support.

Either the participant and the companion will be instructed in the general and individual characteristics of both physical and cognitive programs (VIVIFRAIL-COGN). Also, all participants will receive instructions, printed materials and audiovisual support of the cognitive sessions with the VIVIFRAIL-COGN material.

Table 4 shows the recommended distribution of both the physical and cognitive components of the intervention. Adherence to the cognitive training program will be registered together with the exercise in the VIVIFRAIL booklet.

**Table 4 Tab4:** Recommended distribution of exercise and cognitive training sessions per week

	**Monday**	**Tuesday**	**Wednesday**	**Thursday**	**Friday**	**Saturday**	**Sunday**
Morning	VIVIFRAIL Wheel	Walk	VIVIFRAIL Wheel	Walk	VIVIFRAL wheel	Walk	Rest
Afternooon		Cognitive training		Cognitive training			

### Outcome measures

#### Primary outcome

The primary outcome is the change in the number of auto-reported falls during the study period. Falls, number of falls and its consequences will be registered by the participants /relatives /caregivers with a diary register according with ProFANE group (Prevention of Falls Network Europe) recommendations on reporting of fall prevention programs’ outcomes [62, 82]. Participants/relatives/caregivers will be instructed to use the diary register (Additional File 3) and will be reviewed by the investigator team during T0, T1 and T2 assessments. During follow-up (6, 9 and 12 months after the start of the intervention) a telephone call and a review of the electronic clinical chart will be conducted to register falls and associated events.

#### Secondary outcomes

The secondary measures will be assessments that evaluate fall-related constructs such as fall-related healthcare system utilization, cognitive and physical capacities, psychological and muscle size and quality by echography. Additionally, instrumented measurements of frailty-related kinematic parameters will be performed during the physical performance measures by using inertial sensors (Table 1).

#### Fall-related outcomes

In addition to fall occurrence along 1-year follow-up, in this study, we will assess a set of core outcomes recommended by the ProFANE initiative and that have been poorly reported in previous studies [68, 82]. During follow-up and telephone visits, fall-related healthcare system use (contacts, admissions, emergency visits) and central/peripheral fall-related fracture (radiologically confirmed) will be ascertained and later confirmed by medical records check. In addition, fall related psychological consequences will be assessed through the assessment of the presence of fear of falling [83]. Health-related quality of life (HRQoL) will be measured through the Spanish version of the EuroQoL-5D [84]. Physical activity levels will be evaluated through the Spanish version of the Brief Physical Activity questionnaire [85].

### Fall risk

An increased risk of falling will be considered according to national and international recommendations (one or more of the following criteria): 2 or more falls or 1 fall with medical attention in the last twelve months or a significative gait disorder assessed by performance tests (TUG > 20 s and or UGS test < 0.8 m/s) [14, 86]. The TUG test is a classic test to assess risk of falls. Participant must raise from a chair without help, walk three meters, turn back and sit again. A time of > 20 s is indicative high risk of falls [87].

### Physical function endpoints

Physical function of the participants will be evaluated by the SPPB [88], which evaluates, balance, gait ability and leg strength using a single tool. Total score ranges from 0 (worst) to 12 points (best). The SPPB validity for frailty screening and predicting disability, institutionalization and mortality. A total score of less than 10 is deemed indicative of frailty and a high risk of disability and falls. A 1-point change in SPPB is deemed a meaningful clinical change [89].

Isometric handgrip strength will be measured using a manual dynamometer in two attepms in both dominant and non-dominants hands. The best of both will be recorded. Handgrip asimmetry has recently been proposed as a early marker of future falls [90].

Maximal dynamic lower limb strength (in kilograms) will beassessed using the 1 repetition maximum (1RM) test in the bilateral leg press exercise using exercise machines (Matrix, Johnson Health Tech, Ibérica, S.L., Torrejón de Ardoz, Spain; and Exercycle S.L., BH Group, Vitoria, Spain). In the first assessment, subjects will be instructed on the exercise execution and they will warm-up with specific movements for the leg press. Subject’s maximal load will be established in no more than five attempts, with a recovery period lasting 3 min between attempts. After the 1RM values are determined, the maximal power output will be measured (in watts) by the performance of 10 repetitions at maximal velocity at an intensity of 50% of 1RM by using a linear velocity transducer connected to the weight plates (Vitruve linear Encoder System,Vitoria, Spain). During all neuromuscular performance tests, strong verbal encouragement will be given to each subject to motivate them to perform each test actionas optimally and rapidly as possible.

### Sarcopenia-related measures

Sarcopenia clinical probability will be measured using the definition proposed by the European Working Group on Sarcopenia in Older People (EWGSOP) [91]. In these criteria clinical suspiction is present in subjects with a > 4 in the SARC-F scale, and probable sarcopenia is confirmed with a 5-repetition chair test time > 15 s or a dominant handgrip strength < 27 kg in men or < 16 kg in women. Muscle quality (echo-intensity) and size (muscle thickness) of the rectus anterior muscle and eminence thenar will be assessed with a portable ultrasound system (Philips Healthcare Lumify C5-2 Transductor, Philips Ultrasound, Bothell, WA,USA) operated by a trained member of the researcher’s team [92].

### Fracture risk

Risk of fracture will be assessed with the Garvan fracture risk calculator (https://www.garvan.org.au). This tool allows to estimate 5- and 10-years fracture risk by equations based on anthropometric data, previous fractures since the age of 50, falls in the last year and optionally bone mineral density data. It has been validated very recently in Spanish population [93].

### Neuropsychological assessment

The MoCA [80] test will be used to assess changes in cognitive function and to individualize cognitive intervention. MoCA has been explained in detail before (see paragraph B2). The Trail Making Test (TMT), part A, will be used to assess executive function. In TMT-A, the participant is asked to connect randomly arranged circles containing numbers from 1 to 25 following the number sequence, and doing it as quickly as possible [94]. Mood will be assessed through the Yesavage GDS [95], a 15-item scale used to screen for depressive symptoms in older adults.

### Dual-task GS

Worsening of the performance in the GS while performing a dual-task test (dual-task cost) may be early predictors of fall risk, and may be useful tools for functional evaluations in frail older patients. The dual-task paradigm will be used in the 5-m usual GS. Two trials will be conducted to assess GS while the patient is performing a verbal fluency and a counting task (verbal GS and arithmetic GS, respectively) [96, 97]. Participants will be instructed to walk one trial over 5-m as a single-task.

During the verbal dual-task condition (verbal GS), we will measure GS while participants are naming animals aloud. During the arithmetic dual task condition (arithmetic GS), we will assess GS while participants are counting backwards aloud from 100 in ones. Besides the dual task-cost (relative increase in time to complete the 5-m walk under dual-task conditions with respect to single-task), the cognitive accuracy will be measured by counting the number of animals named (dual-task with verbal performance) or determining how many numbers were correctly counted backwards (dual-task with arithmetic performance).

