**Secondary outcomes**							
Risk of falls Usual Gait Speed (UGS) Time up and Go (TUG)	X			X			
Short Physical Performance Battery (SPPB)		X	X	X			
Barthel index (BI)	X		X	X	X	X	X
Frailty Linda Fried criteria	X			X			
Montreal Cognitive Assessment (MoCA)		X	X	X			
Garvan fracture risk calculator		X		X	X	X	X
Yesavage GDS Scale		X		X	X	X	X
UGS with dual tasking		X	X	X			
Clinical criteria of sarcopenia		X		X			
Maximal isometric force of handgrip, knee extension and hip flexion		X	X	X			
Fear of falling (STAC)		X		X	X	X	X
Quality of life (EQ-5D)		X		X	X	X	X
Previous lifestyle		X					
Trail Making Test (TMT – Part A)		X	X	X			
1RM (Leg press)		X	X	X			
Muscular power at 50% 1RM in leg press		X	X	X			
Polypharmacy		X		X	X	X	X
Cumulative Illness Rating Scale for Geriatrics (CIRS-G)		X					
Mini Nutritional Assessment Test (MNA)		X					
Acceleration data: gait kinematic parameters (regularity, variability, cadence), Five Times Sit to Stand Test (peak power, impulse) and balance parameters (power spectrum, area)		X	X	X			
Muscular Echo intensity and thickness (ultrasound)		X		X			
Mortality		X	X	X	X	X	X
Admissions to emergency room and hospitalizations		X	X	X	X	X	X
Institutionalization		X	X	X	X	X	X

The multidisciplinary research team have well-known previous experience in functional geriatric assessment and in the prescription of exercise in frail aged participants in different clinical settings [71, 75, 76].

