Nowadays healthcare actions to prevent falls in frail older persons with high risk of falling remain scarce, isolated and usually fragmented, despite the efforts that are being made by policymakers, reflected in the recent availability of evidence-based public national/international recommendations [12, 73, 86]. In those recommendations, physical exercise appears as the most evaluated intervention. It is very well known that it is an effective and safe intervention to reduce risk and rate of falls [37, 41, 42]. Our research group very recently showed that the VIVIFRAIL program (www.vivifrail.com) [75] is feasible and effective to improve functional capacity in frail older persons with cognitive problems [72] but we did not explore its potential in falls prevention. It is possible that more integrated and multidomain interventions, as proposed in the present study protocol, are needed in the case of frail older persons. Specifically, if our hypothesis is correct and we show that VIVIFRAIL-COGN intervention is more effective in terms of rate, risk of falls and functional improvement in this population, a new therapeutic window is opened: falls and risk of falls may be improved (and potentially the burdensome consequences of falls, such as fractures) through combined physical-cognitive interventions.

One of the strengths of our study is the multidisciplinary nature of the project (geriatricians, physiotherapists, occupational therapists, psychologists, nurses). This is a remarkable opportunity to establish new protocols and share our results with the scientific community and healthcare professionals with interest in frail older persons with high risk of falling.

Another important aspect of our study is the non-exclusion of frail older patients with cognitive problems. Falls are very prevalent in cognitive decline frail older persons and cognitive decline it is a very well-known risk factor of falling and fractures. The non-exclusion of frail participants with high risk of falling and cognitive problems improves external validity and makes the trial unique in comparison with previous trials in this research area.

In summary, this trial will provide new evidence about the effectivity of an individualized multidomain interventions on falls by studying the effect of additive effects of cognitive training and physical exercise to prevent falls in older frail persons with high risk of falling.

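### The dual-task cognitive score is a raw count of answers over a fixed 5-m walk, so at an equal answering rate it falls as gait gets faster and rises as gait slows

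*Protocol article*

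**What the plan says.** The Dual-task GS section fixes a distance: "The dual-task paradigm will be used in the 5-m usual GS". In the verbal condition "we will measure GS while participants are naming animals aloud"; in the arithmetic condition "we will assess GS while participants are counting backwards aloud from 100 in ones". Two results come from each walk.

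- **Motor side:** the dual-task cost, defined as the "relative increase in time to complete the 5-m walk under dual-task conditions with respect to single-task".
- **Cognitive side:** "the cognitive accuracy will be measured by counting the number of animals named (dual-task with verbal performance) or determining how many numbers were correctly counted".

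The motor result is scaled to a single-task reference. The cognitive result is a plain count: the section gives it no fixed answering time, no division by walk time and no single-task reference. Table 1 lists the assessment among the secondary outcomes as "UGS with dual tasking", at T0, T1 (6 weeks) and T2 (12 weeks).

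**The concern.** The walk ends at a distance, not at a time. A participant who covers the 5 m sooner has fewer seconds in which to answer, so the count mixes two things: how fast the participant answers and how long the walk lasts. Calling it accuracy does not help, because it has no denominator of time or of attempts.

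Walk time is not a nuisance that randomisation balances. It is measured after randomisation, and the programme contains gait and balance training. The Discussion hypothesises that the "VIVIFRAIL-COGN intervention is more effective in terms of rate, risk of falls and functional improvement in this population". If gait speed improves more in one arm, the count in that arm is pulled down for a reason unrelated to cognition. What is at stake is whether a change or a between-arm difference in this count can be read as a cognitive result.

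**Working it through.** The documents give no power, effect size or expected value for this count, so there is no figure of the plan to reproduce. The check is arithmetic on the scoring rule.

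**Inputs**
- Distance: 5 m (Dual-task GS section).
- Gait speeds: illustrative, 0.5 to 0.9 m/s. The documents give no dual-task speed. The range is guided by the eligibility cut-off of 0.8 m/s for usual gait speed and by the 0.5–0.8 m/s band for program B in Table 2.
- Gain in speed: 0.1 m/s, an assumption; 0.05 m/s is also shown.
- Answering rate *r*: not in the documents. It is taken as constant within a walk and cancels from the percentages.
- Answers are counted only during the walk (implied by the text).

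**Formulas**
- Walk time = 5 / speed.
- Expected count = *r* × 5 / speed.
- Change in count at equal *r* = (old speed / new speed) − 1.
- Rise in *r* that leaves the count level = (new speed / old speed) − 1.

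**Results**

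| Speed (m/s) | Walk time (s) | Count at equal rate | Rate rise to break even |
|---|---|---|---|
| 0.5 to 0.6 | 10.00 to 8.33 | −16.7% | +20.0% |
| 0.6 to 0.7 | 8.33 to 7.14 | −14.3% | +16.7% |
| 0.7 to 0.8 | 7.14 to 6.25 | −12.5% | +14.3% |
| 0.8 to 0.9 | 6.25 to 5.56 | −11.1% | +12.5% |

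With a gain of 0.05 m/s from 0.6 m/s the count falls 7.7%, and the break-even rise is 8.3%.

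**In answers.** For 0.6 to 0.7 m/s the expected count goes from 4.17 to 3.57 at 0.5 answers/s, from 8.33 to 7.14 at 1 answer/s, and from 12.50 to 10.71 at 1.5 answers/s. The percentage is the same each time.

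**Both abilities improve.** Let speed go from 0.6 to 0.7 m/s.
- Rate up 10%: (0.6 / 0.7) × 1.10 = 0.943, so the count falls about 6% (8.33 to 7.86 at a starting rate of 1 answer/s).
- Rate up 20%: (0.6 / 0.7) × 1.20 = 1.029, so the count rises about 3% (8.33 to 8.57). The direction is right, but the size is far below the true 20%.

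**Slowing.** From 0.7 to 0.6 m/s at an equal rate, 8.33 / 7.14 = 1.167, so the count rises 16.7% with no cognitive change.

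**Between arms.** The ratio of expected counts equals the ratio of answering rates divided by the ratio of speeds. If the arms have equal speeds, the between-arm comparison is not distorted; otherwise it is distorted by the full speed ratio.

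**With the rate as score.** Count / walk time = *r*. At a constant answering rate the change is 0% at every speed, and rises of 10% and 20% show as 10% and 20%.

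**The case against.** **It may be data capture rather than an endpoint definition.** The section can be read as saying only what is recorded. No analysis of the count is specified, and the derived variable could be settled in an analysis plan that is not shown. This has some force, and nothing in the text prevents dividing by time later. But the sentence says how the quantity is measured, and a reader who follows it obtains the raw count. That is a stated rule that misleads if followed, not a detail left open. The section also cites references for the test procedure; they are not at hand and settle nothing either way.

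**The count is a minor component.** Table 1 names only gait speed under dual tasking, and the section presents the gait side as the predictor of falls. This stands and limits the importance of the point.

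**The direction is conditional.** A reader might infer that anyone who walks faster must score worse, or that anyone who slows will appear to improve. Neither follows. The programme trains divided attention and processing speed (Table 3), so the answering rate may rise enough to offset a faster walk; in a participant who declines, the rate may fall as well.

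**Cognition is measured elsewhere.** A reader might also infer that the trial could report a cognitive loss when cognition is unchanged or better. The documents do not support that at trial level. The MoCA and the TMT-A are scheduled at T0, T1 and T2 and do not depend on walking time, so this count alone would not carry such a claim.

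**The magnitudes are illustrative.** Correct: they show how strongly the score depends on speed, not the bias to expect in this trial.

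**Conclusion.** The point holds as a scoring fault in one component of the secondary dual-task assessment. At an equal answering rate the count is inversely proportional to gait speed: for an assumed gain of 0.1 m/s it is 11% to 17% lower across the speeds shown. A difference over time, or between arms whose speeds differ, therefore cannot be interpreted without walk time.

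The conclusion rests on three assumptions: answers are counted only during the 5-m walk, the answering rate is roughly constant within a walk, and the speeds used are plausible for this population. The direction of the observed change remains open if the answering rate changes too. The primary fall rate, the dual-task cost, the MoCA and the TMT-A are not affected. The correction is still worth making, because it is simple and concerns the interplay of gait and cognition on which the trial's rationale is built.

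**What to change.** In the Dual-task GS section, replace the count as the cognitive score by correct responses per second of dual-task walk time: correct animals per second for the verbal walk and correct numbers per second for the arithmetic walk, each at T0, T1 and T2. State that answers are counted from the start to the end of the 5-m walk. Keep the raw count as a descriptive item only.

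The cost is a short addition to the text, fixed before the analysis. The dual-task walk time is already needed for the dual-task cost, so there is no extra work at the sites, and the rate can be derived for participants already assessed if counts and times were recorded. The change does not make the measure more precise: over walks of this length the counts are small (about 4 answers at 0.6 m/s and 0.5 answers/s). If answering slows during the walk, dividing by time would favour shorter walks somewhat, so the rate should be reported alongside the walk time.
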